### 2.4. Measures and Data Collection Tools

Overall, data will be collected through questionnaires and audio/video recording. Outcome measures will gather quantitative data on the symptoms, quality of life, level of loneliness, family carers’ burden, and mutuality and will be administered at session “0”, at the final session and follow-up (week 2 and week 24), whilst target complaints will be repeated daily and used for the time series analysis. All the measures and related administration time points are shown in Table 1 and described below.

The Neuropsychiatric Inventory Questionnaire (NPI) was developed by Cummings et al. [73] and validated by Binetti et al. [74] for the Italian population and by Zepeda et al. [75] for the Mexican population. It measures the behavioural symptoms related to dementia conditions, assessing twelve sub-domains: delusions, hallucinations, agitation/aggression, depression/dysphoria, anxiety, elation/euphoria, apathy/indifference, disinhibition, irritability/lability, motor disturbance, night-time behaviours, and appetite/eating. Additionally, a caregiver distress scale was included for measuring the psychological impact of the neuropsychiatric symptoms on family caregivers [76]. The NPI anxiety (NPI-A) score will be used to assess the level of anxiety of participants at pre/post treatment. The test has good internal consistency, content validity, and inter-rater/test-retest reliability.

The clinical dementia rating (CDR) is a multidimensional tool that measures the level of cognitive and functional impairment from the patient and proxy point of view. The information is collected by independent semi-structured interviews. Assessed domains include: memory, orientation, judgment and problem solving, community affairs, home and hobbies, and personal care. The score ranges from no impairment to severe dementia on a five-point scale. For the purpose of this project, the “sum of the boxes” (SOB) scoring method will be used: each domain box scores are summed, giving the possibility to differentiate between very mild (3–4) and mild dementia (4.5–9). CDR is widely used in research for its well-established validity and reliability [77,78]; additionally, the CDR-SOB method gained good reliability [71,79] and reputable use of its indexes of severity in therapeutic trials [80]. In this research, CDR will be used to assess the level of dementia at the recruitment phase, then to observe any natural progression of dementia, as a confounded variable at follow-up.

The geriatric depression scale (GDS) is a screening tool consisting of a 30-item questionnaire for measuring symptoms of depression in older people. Its cut-off score is 9/30 and mild depression ranges between 10–19, whilst severe depression between 20–30. It is widely used in research and clinical settings because of its sensitivity (92%) and specificity (89%). GDS seems reliable to detect depression in mild-to-moderate dementia, depending on the level of insight of the person; therefore, it needs caution in administration [72].

The target complaints (TC) daily form [81] is a co-constructed self-report measure of three central idiosyncratic issues and one general wellbeing item. The items are identified together with the therapist at session “0”, then rated daily on a Likert-scale, from 1 to 10, where 1 equals “not bothered at all” and 10 equals “could not be worse”. Each complaint should be concrete, measurable/quantifiable, frequent, stable without treatment, relatively independent from one another, specific, and negatively formulated. The main instruction that helps identifying and scoring the target complaints is “Please record up to three presenting concerns that brought you to therapy. Circle the number that best represents your personal degree of discomfort as a result of each issue.” Improvement on global assessments and target complaints correlated at 0.71 [82], and test-retest reliability was at 0.76 [83].

The University of California, Los Angeles loneliness scale version 3 (UCLA-LS3) is a 20-item, self-reported questionnaire, broadly used to measure subjective feelings of loneliness and social isolation in various populations, including older adults and people with dementia. UCLA-LS3 has a well-established validity and reliability for its use in different languages, among which are Italian and Spanish [84,85,86]. The scale will be used to assess whether loneliness is a present factor and to observe whether regular contact with the therapist, rather than treatment, can influence this secondary variable and, thus, the level of depression (primary variable).

The quality of life-Alzheimer’s disease (QOL-AD) is a self-report tool for the PWD and their proxy/caregiver, based on 13 items of multiple domains, including physical health, mood, marriage, and fun. QOL-AD has excellent internal consistency and inter-rater reliability, as well as good criterion and construct validity [87].

The Ad-hoc common assessment tool is a questionnaire aimed at obtaining information on the level of care required by the PWD. It is an idiosyncratic and non-standardised tool, containing questions such as the weekly hours of caregiving and type of formal or informal support involved.

Zarit burden inventory (ZBI) measures the level of caregiver burden and is widely used in dementia research for its good validity and internal consistency reliability (Cronbach’s alpha coefficient of 0.92) [88,89]. The revised version contains 22 items, each one endorsed on a five-point scale, ranging from 0 (never) to 4 (nearly always). It provides a total score; recently, the author identified subdomains and related scores using a concept mapping method. Subdomains are: burden in the relationship, emotional well-being, social and family life, finances, loss of control over one’s life (scaling and scoring version 6.0 [90]).

The mutuality scale [91] is a self-report questionnaire that measures the construct of mutuality, as defined by the authors: “the positive quality of the relationship between caregiver and care-receiver” (p. 376). The scale consists of 15 items, divided in subdomains (love, shared pleasurable activities, shared values, and reciprocity), rated on a five-point scale, ranging from 0 (not at all) to 4 (a great deal). High scores indicate high mutuality, which is associated with decreased caregiver’s stress [91,92,93] and lower caregiver burden [94].

Clinical outcomes in routine evaluation–outcome measure (CORE–OM) is a 34-item self-report measure of psychological distress, comprising of four domains: wellbeing, symptoms, functioning, and risk [95]. CORE–OM is widely used in psychotherapy research and clinical settings for its good reliability and test-retest stability [96]. A study on the older adult population reported that the tool can be used with people with mild cognitive difficulties and recommended the use of cut-off points, identified by the latter investigation, due to the risk of false positives [97].

The Gestalt therapy fidelity scale (GTFS) [98] is a 25-item tool assessing the treatment fidelity on a 25-min videotape of GT sessions. Video recordings are randomly selected at the end of the first treatment, and external assessors evaluate whether the treatment is Gestalt or not by scoring each item using a “yes” or “no” rate. In the case that an intervention falls under the cut-off score of 11, the therapist will be excluded from the research, and the intervention will be considered null for the purposes of this study.

### 2.5. Data Analysis

Continuous variables will be analysed and reported as mean ± SD (standard deviation) or median and IQR (interquartile range), on the basis of their distribution (assessed through Shapiro–Wilk test). Discrete variables will be reported as absolute frequencies and percentage.

In order to evaluate any pre/post improvements (from baseline to follow-up: at the final session, after two weeks and twenty-four weeks following the end of the treatment) in the main outcomes, i.e., depression and anxiety symptoms (GDS; NPI-A), quality of life (QOL-AD), and the therapy outcome (CORE–OM), three types of analysis will be carried out: (a) visual analysis, comparing the target complaint (TC) scores during the three phases; (b) mean difference from baseline to follow-up tested, by means of paired t-test or Mann–Whitney U test, according to the distribution of the outcome variable [99]; (c) mean baseline reduction (MBLR) for obtaining the effect size for single-case designs [100,101,102], as follows:MBLR = (Mean of Baseline phase − Mean of Follow-up phase) × 100/Mean of Baseline phase.(1)

The same procedure will be applied for the secondary outcome, i.e., loneliness. Additionally, data collected from family caregivers (i.e., QOL-AD family version, caregiver burden scale, and the mutuality scale) during the three phases of the study will be compared with subjects’ outcomes, in order to evaluate indirect effects of the treatment, by means of Pearson or Spearman correlation coefficients, as appropriate.

Blind raters will assess the fidelity of the approach by rating a small sample of sessions through the GTFS.

A two-tailed *p* value < 0.05 will be considered significant. Data will be analysed using SPSS for Windows V24.0 (SPSS Inc., Chicago, IL, USA) and Simulation Modeling Analysis (SMA) for Windows V07.30.20 (ClinicalResearcher, Jeff Borckardt, Medical University of South Carolina).

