### 1.5. Proposed Research Aims and Objectives

The general objective of the research is to determine whether or not GT is an effective treatment for depression in PWD.

Specific objectives of the study are:-To assess if there is a pre/post improvement and, if so, how great this is (clinical significance), according to the outcome variables rates, as well as whether it can be attributed to the therapy intervention.-To assess if study participants suffer with loneliness.-To assess if loneliness is mitigated by the regular contact with the therapist.-To assess if the regular contact with the therapist affects the level of depression.-To assess if a clinical improvement of depression symptoms has an indirect effect on the level of family carers’ burden.-To assess if a clinical improvement has an indirect effect on the mutuality of the relationship between the patient and the family carer.

In order to achieve the objectives, the following research questions will need to be answered:Is there any pre/post treatment improvement?If the answer to question 1 is yes, is the change clinically significant (reduction of symptoms by 50%)?If loneliness is a factor, is the improvement solely due to the social contact with the therapist? ORCan the improvement be attributed to the therapy intervention?Can the improvement of the patient also have an impact on the caregiver’s burden and level of mutuality?

The researchers hypothesised that: depressive symptoms will improve post GT treatment and the improvement will be maintained at follow-up; the level of loneliness, if a factor, can decrease post-treatment and remain so at follow-up; the improvement of symptoms is related to the GT treatment; the level of burden of the family carer will reduce whilst the mutuality in the relationship will increase as the PWD’s depression improves.

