## 2. Materials and Methods

### 2.1. Research Design

The ABA single-case experimental design will be used for the purpose of the study, as explained previously.

The research method is divided into three phases: an “A” baseline period of two weeks between the assessment session “0” and initial psychotherapy session; a “B” intervention period of minimum eight GT sessions; an “A” follow-up period of six months after the end of the intervention, with measurements at the final session, after two weeks and six months. More specifically, in relation to data collection, the following will happen in each phase: A—at the baseline, outcome measures will be administered at session “0”, and individual target complaints (TC) will be recorded daily for the following two weeks; B—in the intervention phase, target complaints will be completed daily; A—in the follow-up phase, participants will continue with daily assessment for another two weeks, while outcome measures will be administered at the final session, i.e., week two and week twenty-four (Figure 1).

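### The plan hypothesises that improvement is maintained at follow-up, but its tests for depression and loneliness are all anchored on baseline and so do not test maintenance

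*Protocol article*

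**What the plan says.** Section 1.5 states two hypotheses about time for depression: "depressive symptoms will improve post GT treatment and the improvement will be maintained at follow-up". The parallel statement for loneliness is that "the level of loneliness, if a factor, can decrease post-treatment and remain so at follow-up".

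Section 2.5 gives three types of analysis for the main outcomes, applied to the time points "from baseline to follow-up: at the final session, after two weeks and twenty-four weeks following the end of the treatment", and uses the same procedure for loneliness:

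- a "visual analysis, comparing the target complaint (TC) scores during the three phases";
- a "mean difference from baseline to follow-up tested, by means of paired t-test or Mann–Whitney U test", with the rule that a two-tailed p "value < 0.05 will be considered significant";
- an effect size, "MBLR = (Mean of Baseline phase − Mean of Follow-up phase) × 100/Mean of Baseline phase".

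GDS and UCLA-LS3 are scheduled at session 0, the final session, week 2 and week 24 (section 2.4 and Table 1). For the daily target complaints, section 2.1 says that after therapy "participants will continue with daily assessment for another two weeks".

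**The concern.** Maintenance is half of the depression hypothesis and an evident purpose of the six-month visit. It is a statement about what happens between the end of therapy and week 24. The tests and the effect size for GDS and UCLA-LS3 instead ask what happened between session 0 and a later visit. A significant baseline-to-week-24 result is compatible with a gain fully kept, with half of it lost, and with most of it lost.

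Loss after therapy is a live possibility on the plan's own terms. It asks whether improvement may be due only to contact with the therapist, which stops when therapy stops. It also repeats the Clinical Dementia Rating to observe progression at follow-up.

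The opposite misreading is possible too. A gain that is fully kept can look lost because the week-24 test happens to miss p < 0.05, although the difference between the two visits was never examined.

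**Working it through.** **1. Hypothesis against analysis**

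| Stated analysis | Variable | Reference | Does it compare week 24 with the final session? |
|---|---|---|---|
| Visual analysis | Target complaints only | Across phases | Not clearly: daily ratings run two weeks after therapy (2.1); Table 1 says until the follow-up session, without saying which |
| Significance test | GDS, UCLA-LS3 and others | Baseline | No |
| Mean baseline reduction (MBLR) | GDS, UCLA-LS3 and others | Baseline | No; no criterion for how much must be kept |

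For week 24 the tested null is: mean at week 24 = mean at baseline. The null that bears on maintenance concerns the mean at week 24 minus the mean at the final session. The second is not stated.

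**2. Inputs**

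- Sample size: 12 (section 2.3). This agrees with the upper end of the recommended 4 to 10 cases plus 20%: 10 × 1.20 = 12. After the stated 20–30% dropout, 12 × 0.80 = 9.6 and 12 × 0.70 = 8.4, so about 8 to 10 remain. I use 12 and 9 (25% dropout).
- Alpha: 0.05, two-sided (section 2.5).
- Gain at the final session: not given. Assumed 7.25 points (the plan's 50% reduction applied to 14.5, the midpoint of GDS 10–19) or a smaller 4 points.
- SD of within-person change: not given. Assumed 4, 5 or 6, the same for every pair of visits (independent occasion errors, each with SD of change/√2).
- Half the gain is lost by week 24.

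**3. Chance that week 24 is still significant against baseline**

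For a paired t-test, the noncentrality is δ = (remaining gain / SD) × √n, and the chance of a significant improvement is P(T > t0.975, n−1) for a noncentral t with n − 1 degrees of freedom.

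Example with n = 12, SD 5 and a gain falling from 7.25 to 3.625: δ = (3.625/5) × √12 = 2.51, critical value 2.201, probability 63%.

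**4. Chance that both the final-session and the week-24 tests are significant, half the gain lost** (simulation, 100,000 trials per cell)

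| Gain at final session | N | SD 4 | SD 5 | SD 6 |
|---|---|---|---|---|
| 7.25 points | 12 | 82% | 63% | 48% |
| 7.25 points | 9 | 66% | 48% | 35% |
| 4 points | 12 | 34% | 22% | 15% |
| 4 points | 9 | 24% | 15% | 10% |

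Opposite case, a 4-point gain fully kept: significant at the final session but not at week 24 in 8% to 17% of trials with 12 participants, and 14% to 18% with 9.

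**5. What MBLR would show in the 7.25-point example**

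- Final session: 7.25 × 100/14.5 = 50%.
- Week 24: 3.625 × 100/14.5 = 25%.
- If final session, week 2 (gain still full) and week 24 are averaged as one follow-up phase: mean gain (7.25 + 7.25 + 3.625)/3 = 6.04, so MBLR = 6.04 × 100/14.5 = 42%.

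Reported by visit, MBLR shows the loss. Pooled, it largely hides it. The formula does not say which is meant.

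**6. Precision of the missing contrast**

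Half-width of the 95% interval for final session to week 24 = t0.975, n−1 × SD/√n:

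| N | SD 4 | SD 5 | SD 6 |
|---|---|---|---|
| 12 | 2.5 | 3.2 | 3.8 |
| 9 | 3.1 | 3.8 | 4.6 |
| 8 | 3.3 | 4.2 | 5.0 |

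A loss of half of 7.25 points is 3.6 points, so several of these intervals would include zero even if the estimate fell exactly on the true loss.

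**The case against.** A reader might infer that the plan will often declare a group to have kept its gain when half is gone. The documents do not support that. Section 2.5 contains no rule that two significant baseline tests mean maintenance; it says only that improvements from baseline will be evaluated. The percentages above describe a reading that someone might make, not a decision the protocol has fixed. *Often* also depends on the assumed effect. The 7.25-point gain treats the threshold for clinical significance as the true group mean, and entry is allowed on anxiety as well as on GDS, so the 14.5 baseline may be too high. With a 4-point gain the joint rate is a minority throughout.

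It is also fair to say that descriptive means and MBLR by visit would reveal a loss, and that in the 7.25-point example week 24 would fall short of the plan's own 50% criterion. For loneliness, remaining decreased can be read as still below the starting level, which is what the baseline test addresses. Finally, this is a condensed article, and a separate analysis plan may add a further contrast.

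Most of this stands and limits the size of the point. It does not remove it. The article does not leave the analysis open: it names the hypothesis, the contrast, the tests, the alpha and the effect-size formula, and the contrast it names answers a different question from the hypothesis. Descriptive figures by visit would show a loss but carry no statement of uncertainty about it.

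A stricter remedy, a required retention of at least 50% of the gain, is not supported either. The documents give no basis for that fraction. With a fully kept 4-point gain such a test would succeed in only about 23% to 44% of trials with 12 participants and 18% to 33% with 9.

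**Conclusion.** The point holds in a limited form. The stated tests and effect size for GDS and UCLA-LS3 can show that some improvement over baseline remains at week 24. They do not test whether the final-session gain was kept, and the visual analysis of target complaints does not clearly reach beyond two weeks after therapy. That conclusion follows from the text and needs no assumption.

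The size does rest on assumptions. With half the gain lost and an SD of change of 4 to 6, both baseline tests are significant in about 10% to 34% of trials for a 4-point gain and 35% to 82% for a 7.25-point gain, with 9 to 12 participants. These figures show how weakly a pair of significant baseline tests speaks to maintenance. They are not the error rate of any rule in the protocol.

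**What to change.** In section 2.5, add for GDS and UCLA-LS3 the within-person change from the final session to week 24, with its 95% confidence interval. State that any conclusion about maintenance rests on that estimate and interval. Describe a significant baseline-to-week-24 test only as showing that some improvement over baseline remained at week 24. A retention fraction is optional; if one is used, fix and justify it in advance.

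The cost is a sentence or two and one extra contrast per scale, on data already scheduled. The drawback is precision: with 8 to 12 completers the half-width is about 2.5 to 5.0 GDS points under the assumed SDs, so maintenance will often have to be reported as uncertain.

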### 2.2. Study Setting and Intervention

The intervention will consist of individual GT sessions, delivered weekly for the duration of one hour each. The minimum number of sessions is eight, whilst a maximum number will be recorded, depending on the individual needs of the participants with dementia.

The intervention will be delivered in psychotherapeutic settings, provided by public health clinics or private therapy centres.

Participants will be provided with an information sheet describing the study purpose and procedure, and they will be asked to sign a consent form for data collection and treatment. The full anonymity of the individuals taking part in the treatment will be ensured, according to the general data protection regulation (2016/679) [69] and national laws on the privacy of sensitive and health-related data, currently in force in Italy and in Mexico. The study protocol will be submitted to the attention of the competent ethics committees.

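### Depression is the primary variable in 1.5 and 2.4, but 2.5 tests four unranked main outcomes at up to three times at an unadjusted 0.05, with no primary time named

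*Protocol article*

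**What the plan says.** Two parts of the protocol article point to a single primary outcome. Section 1.5 states: "The general objective of the research is to determine whether or not GT is an effective treatment for depression in PWD". Section 2.4, describing the loneliness scale, calls loneliness a secondary variable and refers to "the level of depression (primary variable").

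Section 2.5 is organised differently. It sets out to evaluate pre/post improvement "in the main outcomes, i.e., depression and anxiety symptoms (GDS; NPI-A), quality of life (QOL-AD), and the therapy outcome (CORE–OM"), without ordering the four. The post-baseline assessments are "at the final session, after two weeks and twenty-four weeks following the end of the treatment", and none is named as primary. The same procedure is then applied to loneliness as the secondary outcome. A single rule covers every test: "A two-tailed *p* value < 0.05 will be considered significant". No multiplicity adjustment or testing order is mentioned.

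The timing of the final session is open. Section 2.2 sets a minimum of eight weekly sessions, "whilst a maximum number will be recorded, depending on the individual needs of the participants with dementia".

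**The concern.** The sections disagree on what the study is meant to show. On 1.5 and 2.4, success means improvement in depression. On 2.5, a significant change in anxiety, quality of life or general distress stands level with one in depression, and a result at any of three times stands level with any other. The Discussion expects significant data and speaks of evidence of efficacy, so the tests are not offered as purely descriptive.

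With no ranking and no adjustment, 0.05 is the error rate of each test and not of the conclusion. A single significant result could be put forward as evidence of benefit, and nothing in 2.5 says which result was meant to carry that weight.

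A smaller, related issue is that the first post-baseline score is taken at a session whose date is set person by person. If therapy tends to end when someone is doing well, that score is partly selected for being good. There is no control group in the pre/post comparison to reveal this.

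**Working it through.** **Inputs from the article**
- Level: 0.05, two-tailed, no adjustment (2.5).
- Main outcomes: 4 (2.5). Post-baseline times: 3 (2.5). Loneliness, by the same procedure, adds one outcome.
- Participants: 12, with 20–30% dropout allowed for (2.3). Completers: 12 × 0.8 = 9.6 to 12 × 0.7 = 8.4.

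**Assumed, because the article gives no values**
- Correlation of change scores between outcomes: 0 to 0.7.
- Correlation between times: 0.5 to 0.9.

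**Step 1: the plan's own figure.** One two-tailed test at 0.05 has a 5% chance of a false significant result. Half of that, 0.05/2 = 2.5%, lies in the direction of improvement.

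**Step 2: how many tests.** Section 2.5 allows two readings. Its list of three times gives 4 × 3 = 12 tests. Its analysis (b) speaks of baseline to follow-up, and its formula (1) uses a follow-up phase mean, which could mean one test per outcome, or 4 tests.

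**Step 3: independent tests.** The chance of at least one false result among k tests is 1 − 0.95^k in either direction, and 1 − 0.975^k for improvement.
- k = 4: 1 − 0.95^4 = 18.5%; 1 − 0.975^4 = 9.6%.
- k = 12: 1 − 0.95^12 = 46.0%; 1 − 0.975^12 = 26.2%.

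**Step 4: correlated tests.** Simulation of 12 paired t-tests under no true change used 40,000 replicates for each combination of the assumed correlations, at n = 12 and n = 9. Results at the two sample sizes were nearly the same.

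| Tests | Either direction | Improvement only |
|---|---|---|
| One named test | 5% | 2.5% |
| GDS alone at three times (n = 12, correlated) | 8.8–12.7% | 4.4–6.5% |
| Four outcomes, one test each, independent | 18.5% | 9.6% |
| Four outcomes, three times, correlated | 23–42% | 11–24% |
| Four outcomes, three times, independent | 46.0% | 26.2% |

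The independent rows are the upper end, because positive correlation lowers these figures. Only the paired t-test option in 2.5 was simulated.

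**Step 5: the final session.** No calculation is possible from the article. Section 2.2 gives a minimum and says the number depends on individual needs. Sections 2.1 and 2.4 and Table 1 schedule GDS only at session 0, the final session and follow-up. Any link between ending therapy and symptoms would therefore have to run through the daily target complaints or clinical impression. Its strength is not stated.

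**The case against.** Three stronger readings are tempting, and the documents do not support them.

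*That a chance improvement is likely.* A reader may take the 46% for 12 independent tests as that chance. It counts significant worsening as well. For improvement alone the figure is at most about 26%.

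*That the study succeeds if any one of 12 tests is significant.* No such rule is written. The word any occurs in a research question in 1.5 and in the aim in 2.5. The hypothesis in 1.5 is narrower: depressive symptoms improve and stay improved. Requiring GDS to improve at two times together would hold the false-improvement rate at or below 2.5%. Twelve tests is also only one reading of 2.5. What stands is that 2.5 does not carry the narrower hypothesis into a named test, and even one test per outcome gives about 10% if the tests are independent.

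*That the open-ended course of therapy produces a bias of known size.* Quantifying it needs a stopping rule linked to symptoms, and the article has none. Nor does it schedule the weekly GDS that a GDS-triggered ending would require. The possibility remains; a figure does not.

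It is also fair to say that multiplicity adjustment is often left to an analysis plan, which is not shown here, and that the group tests are one of three analyses beside visual analysis and mean baseline reduction. That answers the absence of an adjustment taken by itself. It does not answer the conflict between one primary variable and four equal main outcomes, or the blanket 0.05 rule. Both are in the published text.

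**Conclusion.** The point holds as an inconsistency with a moderate effect on error rates. Depression is primary in 1.5 and 2.4 and unranked in 2.5, no time is primary, and each test is judged at an unadjusted 0.05. With no true change, the chance of at least one false significant improvement rises from 2.5% to about 10% (four independent tests) or about 11–26% (12 tests). That is roughly a four- to ten-fold increase. In either direction it rises from 5% to about 18.5%, or to 23–46%.

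These figures rest on the assumed correlations, on paired t-tests, and on treating any significant main-outcome result as support for the therapy. The article permits that last step but does not prescribe it. Selective timing of the final session is a possible further source of apparent improvement, of unknown size.

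**What to change.** In 2.5, name one confirmatory test: GDS change from session 0 to one already scheduled time, stated in advance, at two-tailed 0.05. Report GDS at the other times, and NPI-A, QOL-AD, CORE–OM and UCLA-LS3 at all times, as secondary, with estimates and confidence intervals and no confirmatory significance claim. This brings 2.5 into line with 1.5 and 2.4.

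Week 24 is the scheduled time least exposed to selective timing of the final session, since a passing good spell at the end of therapy has most time to fade. It is still counted from the end of therapy, and 2.4 itself expects natural progression of dementia to confound follow-up, so the choice should be given with its reason.

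If all 12 tests are to remain confirmatory, a Bonferroni correction would require 0.05/12 = 0.0042 for each. For four outcomes at one time it would require 0.05/4 = 0.0125. With 12 participants, one named test is the better use of the data.

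The cost is a few sentences in 2.5. No visit or assessment is added and the therapy schedule is unchanged. The downside is that fewer results may be called significant.
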